### Follow up of women and infants

All details of delivery, maternal assessments and admission during pregnancy are recorded in the case record form that is accessible through the website. Maternal mortality and morbidity will be specified until date of discharge from hospital and six weeks postpartum. In case of admittance of the baby to the neonatal intensive care, high care, medium care unit or maternal ward, details of this admission are also documented. Neonatal mortality and morbidity will be specified until date of discharge from hospital. We will register the diagnosis at discharge: small for gestational age, hypoglycemia, respiratory distress syndrome, chronic lung disease, meconium aspiration, pneumothorax, apneu, asphyxia, necrotizing enterocolitis, intraventicular hemorrhage, periventricular leucomalacia, neonatal sepsis and neonatal meningitis.

A plan for long-term follow up of the mothers is in preparation. Long-term follow up of children will not be performed, because we do not expect differences between both policies during childhood.

### Outcome measures

#### Primary outcome measure

The primary outcome measure will be severe maternal morbidity, which can be complicated by maternal mortality in rare cases. Severe maternal morbidity will be defined as diastolic BP ≥ 110 mmHg, systolic BP ≥ 170 mmHg, major postpartum hemorrhage, eclampsia, HELLP syndrome, pulmonary edema, trombo-embolic disease and/or abruptio placentae [14]. Major postpartum hemorrhage is defined as blood loss > 1000 ml within 24 hours after delivery [15]. Eclampsia is defined as severe pregnancy induced hypertension or preeclampsia resulting in maternal seizures [16]. HELLP syndrome is defined as a complication of severe preeclampsia involving Hemolysis, Elevated Liver functions, and Low Platelets [17]. Trombo-embolic disease is defined as deep-vein thrombosis, pulmonary embolism or both. Patients will be examined for deep-vein thrombosis byduplex dopplerif thrombosis is suspected from clinical examination. A diagnosis of pulmonary embolism will be confirmed by pulmonary angiography, computed tomography, magnetic resonance imaging or a ventilation-perfusion lung scan [18-20].

#### Secondary outcome measures

Secondary outcomes will be neonatal mortality or neonatal morbidity, caesarean section rate, instrumental vaginal delivery rate, maternal quality of life and quality of recovery and costs. Adverse neonatal outcome will be defined as a 5-minute Apgar score below 7, an umbilical artery pH below 7.05 or admission to the neonatal intensive care.

### Statistical issues

#### Sample size

The aim of induction of labour is to reduce the rate of severe complications of hypertensive disease, such as postpartum hemorrhage, sever hypertension (diastolic BP ≥ 110 mmHg), eclampsia and HELLP syndrome. In women with a singleton pregnancy in cephalic presentation at term (>36 weeks), the prevalence of such complications in 2003 and 2004 was 12% [21]. To our opinion, the disadvantages of induction of labour outweigh the advantages when the complication rate is reduced to 6%. In order to detect such a difference, we will need two groups of 360 patients (two-sided test, alpha .05; beta .80).

#### Data analysis

The analysis will be performed by intention to treat, and stratified for centre, parity and for underlying disease (preeclampsia or pregnancy induced hypertension). Quality of life as well as pain scores will be analysed using repeated measures analysis of variance [22]. Relative risks and 95% confidence intervals will be calculated for the relevant outcome measures.

Moreover, we will evaluate whether the relative benefits of induction of labour will be stronger in women with a ripe cervix at baseline and in women with a short cervical length at transvaginal sonography. In case of equivalence between outcomes, the analysis will be repeated on a par protocol basis.

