**Methods/Design:**

Women with a pregnancy complicated by pregnancy induced hypertension or mild preeclampsia at a gestational age between 36^+0 ^and 41^+0 ^weeks will be asked to participate in a multi-centre randomised controlled trial. Women will be randomised to either induction of labour or expectant management for spontaneous delivery. The primary outcome of this study is severe maternal morbidity, which can be complicated by maternal mortality in rare cases. Secondary outcome measures are neonatal mortality and morbidity, caesarean and vaginal instrumental delivery rates, maternal quality of life and costs. Analysis will be by intention to treat. In total, 720 pregnant women have to be randomised to show a reduction in severe maternal complications of hypertensive disease from 12 to 6%.

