After a patient has given informed consent for participation in the study cervical length will be measured using transvaginal sonography, and vaginal examination will be performed (Bishop score), both to assess cervical ripeness. At study entry all women will have baseline demographic, past obstetric and medical history recorded. After explanation of the study and informed consent, but prior to randomisation, we will perform a baseline measurement for quality of life (SF-36, HADS, EuroQol 6D3L) and additional questions on intervention preparedness and personal experience of the pregnancy. Subsequently, the patient will be randomised to either a policy that aims termination of pregnancy (intervention group) or a policy that aims expectant management for spontaneous delivery (expectant group). Randomisation will be performed through a web-based database which is hosted at the Academic Medical Centre (AMC) in Amsterdam. Randomisation will be 1:1 for intervention and expectant management, and it will be stratified for centre, parity and proteinuria according to the criteria above. Patients fill out additional quality of life questionnaires 6 weeks after delivery and 6 months after delivery (SF-36, HADS, EuroQoL 6D3L, SCL-90) and additional questions on personal experience of the delivery.

At local centres data-collection will be the responsibility of the local research coordinator and the regional research midwives or nurses. The data collected in this study will be coded and processed with adequate precautions to ensure patient confidentially.

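### Quality of life is assigned to repeated measures ANOVA with no stated baseline adjustment; a mixed model with baseline as covariate would be more efficient and keep women with incomplete forms

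*Protocol article*

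**What the plan says.** The Data analysis section fixes the method: "Quality of life as well as pain scores will be analysed using repeated measures analysis of variance". It gives no occasions, model terms or treatment contrast, and no rule for incomplete questionnaires. The same section says of the analysis as a whole: "The analysis will be performed by intention to treat, and stratified for centre, parity and for underlying disease".

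The measurement schedule is in the section on procedures, recruitment, randomisation and collection of baseline data. After consent, "prior to randomisation, we will perform a baseline measurement for quality of life (SF-36, HADS, EuroQol 6D3L", with some further questions. Later, "Patients fill out additional quality of life questionnaires 6 weeks after delivery and 6 months after delivery (SF-36, HADS, EuroQoL 6D3L, SCL-90". SF-36, HADS and EuroQol are therefore scheduled three times, once before and twice after randomisation. SCL-90 is listed only after delivery.

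Quality of life is among the secondary outcomes: "caesarean section rate, instrumental vaginal delivery rate, maternal quality of life and quality of recovery and costs". The Aims section also names its improvement as something the trial will shed light on. The article mentions no baseline covariate, analysis of covariance or mixed model.

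**The concern.** A score taken before randomisation can be used in two ways. As a covariate it removes between-woman variation and sharpens the treatment comparison. As one more outcome occasion in an ANOVA, it adds a time point at which the true group difference is zero by design. A group main effect averaged over that time point understates the postpartum effect. A group-by-time test avoids the understatement but amounts to a comparison of change scores, spread over two degrees of freedom. Leaving baseline out altogether wastes it.

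The classical procedure also needs a complete set of scores for each woman, so one missing form removes all of her data. In an open-label trial, whether a woman returns a form months after delivery may depend on her allocation or on how the birth went. The loss could then bring bias as well as imprecision. At stake is the reliability of a stated secondary question, with a better analysis available from data already scheduled.

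**Working it through.** **The plan's own figure.** The article gives no sample size or power for quality of life. Its only such figure is for the primary outcome: "we will need two groups of 360 patients (two-sided test, alpha .05; beta .80", to detect 12% against 6%. Reading the last value as power, n = [1.960 × √(2 × 0.09 × 0.91) + 0.842 × √(0.12 × 0.88 + 0.06 × 0.94)]² / 0.06² = 356 per group. Power at 360 is 80.4%. The stated figure reproduces and is not in question here.

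**Inputs for quality of life.** From the article: one pre-randomisation and two postpartum occasions, and 360 women per group. Assumed, because the article gives no values: equal variance (set to 1) at each occasion, the same correlation ρ between any two occasions, no difference at baseline, and a constant effect d at both postpartum visits.

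**Size of the main effect.** With baseline as one of three occasions, the group main effect is (0 + d + d)/3 = 2d/3. The group-by-time contrast, postpartum mean minus baseline, is the full d.

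**Efficiency.** This is squared signal over variance, relative to the postpartum mean adjusted for baseline.

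| Quantity | ρ = 0.4 | ρ = 0.5 | ρ = 0.7 |
|---|---|---|---|
| Variance, mean of three occasions, (1+2ρ)/3 | 0.600 | 0.667 | 0.800 |
| Variance, mean of two postpartum visits, (1+ρ)/2 | 0.700 | 0.750 | 0.850 |
| Variance, change from baseline, (1+ρ)/2 + 1 − 2ρ | 0.900 | 0.750 | 0.450 |
| Variance, baseline-adjusted, (1+ρ)/2 − ρ² | 0.540 | 0.500 | 0.360 |
| Efficiency, three-occasion main effect | 40% | 33% | 20% |
| Efficiency, change contrast | 60% | 67% | 80% |
| Efficiency, two postpartum visits unadjusted | 77% | 67% | 42% |

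Example at ρ = 0.4:
- Main effect: (4/9)/0.600 = 0.741, against 1/0.540 = 1.852; ratio 0.40.
- Change contrast: 0.540/0.900 = 0.60.
- Two postpartum visits: 0.540/0.700 = 0.77.

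**Power.** This is for an assumed d = 0.2 SD with 360 per group and no missing forms. The group-by-time figures come from 4,000 simulated trials per correlation.

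| Analysis | ρ = 0.3 | ρ = 0.5 | ρ = 0.7 |
|---|---|---|---|
| Three-occasion main effect (0.133 SD) | 69% | 59% | 52% |
| Group-by-time F test, 2 df | 64% | 79% | 96% |
| Two postpartum visits, unadjusted | 91% | 87% | 83% |
| Baseline-adjusted postpartum mean | 95% | 97% | 99% |

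**Missing forms.** If 20% to 30% lacked the 6-month form and nothing else were missing, a complete-case analysis would lose 0.20 × 720 = 144 to 0.30 × 720 = 216 women. If instead a share m were missing independently at each postpartum visit, 720 × (1 − m)² women would be complete and 720 × (1 − m²) would have at least one postpartum form. That gives 583 against 713 at m = 10%, and 461 against 691 at m = 20%. These rates are illustrative.

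**The case against.** The strongest reply is that the sentence names a family of methods and no more. Repeated measures ANOVA could be run on the two postpartum visits with the baseline score as covariate, or be loose wording for a likelihood-based model that keeps incomplete cases. The schedule calls the first form a baseline measurement and the later ones additional, which fits a covariate as well as an occasion. The sentence also covers pain scores, for which no baseline is described, and SCL-90 has none, so baseline cannot be an occasion for everything it covers. The method carries a citation that cannot be consulted here. A journal article may leave model terms and missing-data rules to a fuller document.

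Much of this stands. A reader might infer that the plan puts baseline in as an occasion, discards women with a missing form and dilutes every quality-of-life comparison. The documents do not support that. No section lists the occasions or sets a complete-case rule, the stated principle is intention to treat, and dilution affects only the group main effect. Nor does the article say how questionnaires are returned or what response is expected.

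The reply does not dispose of the point. The article commits to a method by name, and none of the forms computed above without a baseline covariate matches the baseline-adjusted analysis. The point is therefore to replace a stated method with a better one, not to ask for missing detail. If a baseline covariate is already intended, the efficiency argument falls away and only the handling of incomplete forms remains.

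**Conclusion.** The point holds conditionally. Repeated measures ANOVA without a baseline covariate is a weak choice for this schedule. The main effect falls to two thirds of a constant postpartum effect only if baseline is one of three occasions and the main effect is the treatment test. The undiluted alternatives still lose efficiency: 60% to 80% for the change contrast, and 77% down to 42% for the two postpartum visits alone, as the correlation rises from 0.4 to 0.7. The loss of women applies to the classical complete-case form.

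The efficiency and power figures rest on assumed equal variances, a common correlation and a constant postpartum effect; the power figures also assume 0.2 SD. The counts of lost women rest on assumed missingness rates. A reader might take the point as weakening the trial's main conclusion. It does not: quality of life is secondary, and the primary analysis and sample size are untouched.

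**What to change.** Replace the repeated measures ANOVA for quality of life with a linear mixed model on the 6-week and 6-month scores. Its terms should be treatment, time, treatment by time, the baseline score and the stratification factors the article already names: centre, parity and underlying disease. Omit the baseline term for SCL-90.

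Include every woman with at least one postpartum form, in her randomised group, and report the adjusted difference with its 95% confidence interval at each time. State how a missing baseline score is handled, so that it does not remove a woman who has postpartum data.

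The model has limits. It assumes data missing at random, does not remove bias if response depends on unobserved scores, and cannot use the outcome of a woman who returned no postpartum form. The cost is a change of analysis wording; standard software suffices and no new data are needed.

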Data from the Dutch National Obstetric Registration from Januari 2000 until Januari 2005 show that 38.170 nullipara had a singleton pregnancy in cephalic presentation complicated with pregnancy induced hypertension or preeclampsia. In 18.012 women labour started spontaneously, whereas in 18.810 labour was induced. The non-elective caesarean section rate among women in whom labour started spontaneously was 14% and among women in whom labour was induced this rate was 22% (OR 1,7 95% CI 1,6 to 1,8). The vaginal instrumental delivery rates among these groups were 28% and 24% (OR 0,88 95% CI 0,84 to 0,93).

At present, there is no evidence on the effectiveness and efficiency of induction of labour in women with pregnancy induced hypertension or mild preeclampsia (nearly) at term as compared with expectant management with close monitoring. In post term women and women with ruptured membranes at term, randomised trials have indicated that induction of labour does not increase the instrumental delivery rate [12,13]. However, the fact that the women were post term, might implicate that myometrial gapjunctions facilitating effective contractions were present [12]. These data can not be extrapolated to women who are (nearly) at term with pregnancy induced hypertension or preeclampsia.

In view of this clinical dilemma, we propose a randomised clinical trial in which a policy of induction of labour, if necessary preceded by artificial cervical ripening, is compared with a policy of careful expectant monitoring in women with pregnancy induced hypertension or mild preeclampsia (nearly) at term. At present – to our knowledge – no clinical study has been published or undertaken to investigate this issue.

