### Interventions

#### Intervention group

In the **intervention group**, patients will be induced within 24 hours after randomisation. In patients with a Bishop cervix score > 6 at vaginal examination labour will be induced by amniotomy and, if needed, augmentation with oxytocin. If this score is 6 or lower cervical ripening will be stimulated with use of intracervical or intravaginal prostaglandins according to the local protocol. In case the cervix is judged to be unripe the day after 'priming', the cervical ripening will be repeated. If the cervix remains 'unripe', day 3 will be a rest day. Cervical ripening will be repeated at day 4 and 5. All patients in the intervention group will be monitored clinically until after delivery.

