## Discussion

Pregnancy induced hypertension and preeclampsia are important hypertensive disorders during pregnancy which are associated with increased maternal and neonatal morbidity and mortality. There is no consensus on how to manage mild hypertensive diseases at term. Induction of labour might prevent maternal complications, but is also thought to increase the caesarean and vaginal instrumental delivery rate. This trial is designed to provide evidence on the effectiveness of induction of labour in women with mild pregnancy induced hypertension or preeclampsia (nearly) at term to prevent severe maternal and neonatal complications.

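### The planned cervical-ripeness analysis looks one way, for larger benefit, and names no outcome; it could cheaply be extended to caesarean section, the main harm the protocol names

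*Protocol article*

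**What the plan says.** All places are in the protocol article.

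- **Procedures, recruitment, randomisation and collection of baseline data.** After consent and before randomisation, "cervical length will be measured using transvaginal sonography, and vaginal examination will be performed (Bishop score), both to assess cervical ripeness". Randomisation is stratified for centre, parity and proteinuria, not for ripeness.
- **Intervention group.** The Bishop score decides how labour is induced: "If this score is 6 or lower cervical ripening will be stimulated", and ripening may be repeated over several days.
- **Secondary outcome measures.** Caesarean section rate and instrumental vaginal delivery rate are both listed.
- **Data analysis.** The analysis is by intention to treat, stratified for centre, parity and disease, with relative risks and 95% confidence intervals for the relevant outcomes. Ripeness then enters once: "we will evaluate whether the relative benefits of induction of labour will be stronger in women with a ripe cervix at baseline", and likewise for a short cervical length.
- **Discussion.** Induction "is also thought to increase the caesarean and vaginal instrumental delivery rate". The Abstract and the Background say much the same.
- **Background.** In registry data on nulliparae with these disorders, the "non-elective caesarean section rate among women in whom labour started spontaneously was 14"%, against 22% after induction. Instrumental delivery was 28% after spontaneous onset and 24% after induction.

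**The concern.** The Aims and Sample size sections describe the benefit of induction as less severe maternal morbidity, and operative delivery appears throughout as its cost. Read in that light, an analysis of relative benefits does not naturally cover caesarean section. Yet the protocol ties ripeness directly to how induction is carried out, so caesarean section is an obvious outcome to examine by ripeness.

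If the caesarean excess did differ by ripeness, one pooled relative risk would average over women with a larger and a smaller excess. A null ripeness result for maternal morbidity might then be taken to mean that cervical status is irrelevant, when it would say nothing about caesarean section. An analysis added after the results are known would also carry less weight than one fixed now. Separately, a baseline variable that may predict caesarean section is left out of that comparison.

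**Working it through.** **1. The plan's own figure.** Sample size: "we will need two groups of 360 patients (two-sided test, alpha .05; beta .80" (the .80 is evidently power). The control rate is given as "the prevalence of such complications in 2003 and 2004 was 12"% and the target as "when the complication rate is reduced to 6"%. With pooled variance, mean rate 0.09 and no continuity correction:

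n = [1.96 × √(2 × 0.09 × 0.91) + 0.8416 × √(0.12 × 0.88 + 0.06 × 0.94)]² / 0.06² = (0.7933 + 0.3387)² / 0.0036 = 356 per arm.

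This reproduces 360; power at 360 is 80.4%.

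**2. Information on each outcome.** Assumption: the registry caesarean rates (14% and 22%) stand in for the two arms.

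- Caesareans: 360 × 0.14 + 360 × 0.22 = 130.
- Primary events: 360 × 0.12 + 360 × 0.06 = 65.
- Power for the overall caesarean difference: [0.08 × √360 − 1.96 × √(2 × 0.18 × 0.82)] / √(0.14 × 0.86 + 0.22 × 0.78) = (1.518 − 1.065) / 0.540 = 0.838, that is 79.9%.

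With women split equally by ripeness (180 per cell, assumed) and no true interaction, the standard error of the log-odds-ratio interaction is √[2 × (1/(180 × 0.1056) + 1/(180 × 0.0564))] = 0.55 for the primary outcome. For caesarean section it is √[2 × (1/(180 × 0.1204) + 1/(180 × 0.1716))] = 0.40. Caesarean section is the more informative outcome for a ripeness analysis.

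**3. Interaction power when an 8-point excess is confined to unripe women** (unripe 14% v 22%, ripe 14% v 14%). The unripe share is not given, so it is varied. For a share of 50%, the risk-difference interaction is 0.08 with SE √[(3 × 0.1204 + 0.1716)/180] = 0.0544. The ratio is 1.47 and the power is 31%.

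| Unripe share | Power, risk difference | Power, odds ratio | 95% CI half-width (points) |
|---|---|---|---|
| 50% | 31% | 27% | 11 |
| 70% | 28% | 22% | 11 |
| 80% | 23% | 18% | 13 |
| 90% | 15% | 12% | 17 |

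**4. Stronger gradients.** If the whole-trial excess is 8 points and all of it falls on unripe women, the excess in them is 8 points divided by their share. Risk-difference power is then 81%, 49%, 33% and 18% for the same four shares. With a continuous Bishop score and overall rates held at 14% and 22%, simulation of 720-woman trials gives:

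| Assumed odds ratio per SD, expectant v induction | Interaction power |
|---|---|
| 0.9 v 0.5 | 81% |
| 0.8 v 0.45 | 77% |
| 1.0 v 0.6 | 70% |
| 0.8 v 0.6 | 31% |

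The first three rows imply relative risks of about 0.9 to 1.0 at one SD above the mean score and 2.1 to 2.2 at one SD below. With an assumed expectant rate of 8 to 10% and the same overall relative risk (22/14 = 1.57), those rows fall to about 50 to 68% and the last to about 19 to 22%.

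**5. Covariate adjustment.** Against a wholly unadjusted analysis, power changed from 81.1 to 82.9% (odds ratio 0.6 per SD), 78.6 to 81.0% (0.5) and 80.7 to 85.3% (0.4). The fairer comparator already adjusts for parity. Over that, the gain is about 0 to 5 points for odds ratios from 0.8 to 0.4.

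**6. Instrumental delivery.** The registry difference (28% v 24%) favours induction, and 360 per arm gives about 23% power for it.

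**The case against.** - **The exclusion is inferred from silence.** Data analysis names no outcome for the relative benefits, so caesarean section is neither included nor ruled out; fewer caesareans in ripe women could count as a benefit. This stands, and the point must not be put as an exclusion.
- **A condensed article leaves such detail to the full protocol or analysis plan.** This stands in part: no absence can be charged as a fault. But the article does specify a ripeness analysis, with its modifiers and direction, and that stated choice can be improved.
- **A reader might infer that the trial cannot show which women bear the harm.** The documents do not support this. Ripeness is recorded before randomisation and delivery details are recorded for the women in the trial, so the analysis remains possible. What could be lacking is prespecification and, in most settings, power.
- **A reader might infer that the pooled caesarean result is wrong.** It is not. It is a valid average, and the Sample size section uses no caesarean figure in its weighing of advantages and disadvantages.
- **The two gains need different settings.** The adjustment figures assume that Bishop score predicts caesarean section equally in both arms; the interaction figures assume that it does not. They cannot be added together. This stands.
- **The rates are imperfect.** They are observational, come from nulliparae and compare onset of labour rather than policies, and no rate by ripeness is given. This stands; the figures are illustrations.

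**Conclusion.** The point holds as an inexpensive improvement, not as an error. The stated ripeness analysis is one-directional and has no named outcome, and the article does not say that caesarean section will be adjusted for or examined by ripeness.

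The benefit is modest. Adjustment is worth about 0 to 5 power points. The interaction would be an estimate with a wide interval, not a dependable test: power is about 12 to 31% if an 8-point excess is confined to unripe women, and up to about 80% only under strong assumed gradients at the registry rates. A null interaction must therefore not be read as absence of modification. The case rests on caesarean section; the protocol's own registry figures show no excess of instrumental delivery after induction.

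The size depends on registry rates from nulliparae, an assumed unripe share of 50 to 90% and assumed Bishop-score odds ratios.

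**What to change.** In Data analysis:

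1. Adjust the caesarean section comparison for baseline Bishop score in addition to the stratification factors.
2. State that the ripeness analysis is two-sided and covers caesarean section as well as the primary outcome. Report treatment-by-ripeness estimates with 95% confidence intervals, labelled exploratory, and say that a null result does not show absence of modification.
3. Optionally report instrumental vaginal delivery in the same way, without presuming an excess.

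If the full protocol or analysis plan already says this, one clarifying sentence is enough. The wording should be settled before outcomes by arm are seen. The cost is a few lines of text and one more exploratory interaction estimate, with no new data, visits or patients.
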